## Abstract

**Introduction:**

Platelet-rich plasma (PRP) is a potentially efficacious treatment for ankle osteoarthritis (OA), but its use has not been examined in high-quality studies. Systematic reviews show that PRP injections significantly decrease pain and improve function in patients with knee OA. Ankle OA is more common than hip or knee OA in the young active population; with a prevalence of 3.4%.

PRP injections in ankle OA are shown to be safe and improve quality of life over time, but no randomised controlled trial has been conducted. Our randomised controlled trial will evaluate the efficacy of PRP injections for symptom reduction and functional improvement, compared with placebo, in the treatment of ankle (talocrural) OA.

**Methods and analysis:**

We will conduct the Platelet-Rich plasma Injection Management for Ankle OA study: a multicentre, randomised, placebo-controlled trial. One hundred patients suffering from ankle OA will be randomised into two treatment groups: PRP injection or placebo (saline) injection. Both groups will receive two injections of PRP or placebo at an interval of 6 weeks. Primary outcome is the American Orthopaedic Foot and Ankle Society score at 26 weeks. Secondary outcomes determined at several follow-up moments up to 5 years, include Ankle Osteoarthritis Score, Foot and Ankle Outcome Score, pain subscale of (0–40), Visual Analogue Scale score (0–100), Ankle Activity Score (0–10), subjective patient satisfaction Short Form Health Survey-36, Global Attainment Scaling and the EuroQol-5 dimensions-3 levels utility score. A cost-effectiveness analysis will be performed at 1 year.

**Ethics and dissemination:**

The study is approved by the Medical Ethics Review Committee Amsterdam Medical Center, the Netherlands (ABR 2018–042, approved 23 July 2018) and registered in the Netherlands trial register (NTR7261). Results and new knowledge will be disseminated through the Dutch Arthritis Association (ReumaNederland), Dutch patient federation, conferences and published in a scientific peer-reviewed journal.

**Trial registration number:**

NTR7261.

Strengths and limitations of this studyThis is the first study to evaluate the efficacy and cost-effectiveness of ankle (talocrural) osteoarthritis (OA) in a multicentre, stratified, block-randomised, double-blind, placebo-controlled trial design. A positive study outcome will have a significant effect on widespread availability and nationwide implementation of an intra-articular injection treatment for ankle OA with platelet-rich plasma (PRP). A negative outcome (no effect of PRP), will prevent the widespread use of a non-efficacious treatment on patients.The study population consists only of patients with isolated ankle OA and no concomitant OA in other major joints of the lower extremities that negatively affects their daily activity level.The PRP used in this randomised controlled trial is an available PRP product that is used in clinical practice.There is a multitude of commercial PRP products available that differ in their production method and content, and different treatment regimens regarding dose, timing and number of injections are used in clinical practice. The generalisability to other PRP products and treatment regimens remains unknown.The composition of PRP will not be analysed; this decision was based on the fact that PRP preparation and composition has frequently been analysed and is typically not performed in clinical practice prior to injection.

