### Sample size

Based on previous and ongoing studies, the study protocol of the RCT is designed to detect a difference of 12 points (0–100) on the AOFAS score. There is no official agreement on the minimal clinical important difference for the AOFAS score regarding ankle OA. However in relatable musculoskeletal literature, 10%–15% of the used scale was reported.^13 25 26^ Our predefined minimal clinical important difference of 12% is located within this range.^13 25 26^ Based on a previous placebo-controlled RCT on injection therapy (hyaluronic acid) in ankle OA by De Groot *et al*, an SD of 16.3 can be expected.^6^ Taking into account a two-sided level of significance of 5%, a power of 90% and a dropout rate of 10%, approximately 50 (45 plus 10% drop out) patients per group will be needed (n=100 in total).

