## Discussion

This is the first study evaluating the efficacy and cost-effectiveness of PRP injections in the treatment of ankle OA with a multicentre, stratified, block-randomised, double-blind, placebo-controlled design. The primary outcome is the AOFAS score at 26 weeks. Our study will also evaluate the long-term efficacy of PRP for up to 5 years.

PRP has been shown to alleviate symptoms of patients suffering from knee OA.^11^ In the absence of effective evidence-based non-surgical interventions for ankle OA, PRP would fulfil a clear clinical need. Previous trials concerned with the efficacy of PRP for multiple indications are usually of low quality and adhere to a follow-up of 26 weeks or shorter. Furthermore, a cost-effectiveness analysis has never been performed in previous trials on PRP in the treatment of OA.

A positive study outcome would have a significant impact leading to change in clinical practice, where PRP could be offered as a non-surgical intervention. A negative outcome will prevent the widespread use of a non-efficacious treatment.

This study has potential limitations. First of all, due to financial constraints (semi-quantitative), MRI-defined cartilage degenerative changes will not be used as a secondary outcome score. Furthermore, the composition of PRP is not analysed. This decision is based on the fact that PRP preparation and composition has frequently been analysed and is typically not performed in clinical practice prior to injection.^27^ The PRP we use (Hettich Rotofix32 A centrifuge and Arthrex syringes) is one out of a multitude of commercially available PRP products. All these products differ in their production method and content, and different treatment regimens regarding dose, timing and number of injections are used in clinical practice. The generalisability to other PRP products and treatment regimens remains unknown.

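### The article equates a negative outcome with no effect of PRP, but the trial can at most exclude a benefit of a given size, and some null results would not exclude its own 12-point difference

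*Protocol article*

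**What the plan says.** The strengths-and-limitations list, printed after the trial registration number, foresees two outcomes. A positive one would support wide introduction of PRP for ankle osteoarthritis. For the other it says: "A negative outcome (no effect of PRP), will prevent the widespread use of a non-efficacious treatment on patients". The Discussion has the same pair and states: "A negative outcome will prevent the widespread use of a non-efficacious treatment".

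The Objectives section hypothesises that PRP is efficacious compared with placebo. The Sample size section plans a two-sided 5% test with 90% power for 12 AOFAS points, gives no equivalence margin, and calls 12 points the important difference: "Our predefined minimal clinical important difference of 12% is located within this range". The range meant is 10% to 15% of the scale, and the section concedes that no important difference has been officially agreed for this score in ankle osteoarthritis. On variability it says "an SD of 16.3 can be expected", and on size "approximately 50 (45 plus 10% drop out) patients per group will be needed (n=100 in total").

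The Statistical analysis section says that the authors will interpret blinded results under a cited scheme until they agree, and that the interpretation will not change after unblinding. The Economic analysis section speaks of a positive outcome that is also significant. No inconclusive outcome is described.

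**The concern.** Failure to show a difference is not evidence that there is none. A null result supports a statement such as: a benefit of 12 points or more is excluded. Whether it supports even that depends on the confidence interval. The article attaches a practice consequence to a negative outcome and describes it as no effect, without making that conclusion depend on whether the interval excludes the important difference.

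Two things are at stake. A null result whose interval still reaches 12 points could be reported as evidence against PRP when it is inconclusive by the trial's own yardstick. And even where 12 is excluded, smaller benefits remain compatible with the data, so no effect is still too strong. The Background section says that no well-designed randomised trial of PRP in ankle osteoarthritis has been done, so the wording of a null result would carry weight.

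**Working it through.** **Inputs, all from the Sample size section.** Difference 12 points; SD 16.3; two-sided alpha 0.05; power 90%; 45 evaluable and 50 randomised per group. Differences are PRP minus placebo, so positive values favour PRP.

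**The plan's own figure.** n per group = 2 × (1.960 + 1.282)² × 16.3² / 12² = 38.8, so 39; the t-test version gives 39.8, so 40. The stated 45 before dropout is therefore not reproduced. It equals 40 / 0.9 = 44.4, rounded up, so dropout seems to have been allowed for twice (45 / 0.9 = 50). This makes the trial larger and narrows the window found below. I keep the stated 45. Power for 12 points is then 93.2% (t-test) or 93.7% (normal).

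**Precision with 45 per group.**
- SE = 16.3 × √(2/45) = 3.44
- Half-width of the 95% interval = t(0.975, 88) × SE = 1.987 × 3.436 = 6.83
- Non-significant with a difference in favour of PRP: observed difference below 6.83
- Upper limit below 12: observed difference below 12 − 6.83 = 5.17
- Non-significant but not excluding 12: observed difference from 5.17 to 6.83, a window of 1.66 points
- Highest upper limit of a non-significant result: 2 × 6.83 = 13.7

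**How often this happens.** With true difference θ, P(window) = Φ((6.83 − θ)/3.44) − Φ((5.17 − θ)/3.44).

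| True difference | Non-significant | Non-significant and 12 not excluded | Share of non-significant results |
|---|---|---|---|
| 0 | 95% | 4% | 4.5% |
| 3 | 87% | 13% | 15% |
| 6 | 60% | 19% | 32% |
| 8 | 37% | 16% | 44% |
| 10 | 18% | 10% | 55% |
| 12 | 6.6% | 4% | 65% |

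**Sensitivity.**
- *Evaluable patients.* With 40 per group the window is 4.74 to 7.26; with 50 it is 5.53 to 6.47.
- *Threshold within the cited range.* Against 10 points, the chance of a non-significant result that fails to exclude it is 16% at a true difference of 0 and 39% at 6. Against 15 points it is nil, because the highest upper limit is 13.7.
- *Larger SD (assumption: 20).* The window is 3.62 to 8.38, with chances of 17% at a true difference of 0 and 43% at 6.
- *Smaller effective SD (assumption).* The window closes when the half-width is 6 or less, that is at SD = 6 / (1.987 × √(2/45)) = 14.3. If 16.3 is the SD of the score itself, this needs a baseline correlation above about 0.48 with baseline adjustment (√(1 − r²) = 14.3/16.3), or about 0.61 with change scores (√(2(1 − r)) = 14.3/16.3). The article does not say whether 16.3 refers to scores or changes.

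**The case against.** The strongest reply is that the two sentences describe potential impact and are not analysis rules. A reader might infer that the protocol declares in advance that any non-significant primary test means no effect. The article does not say so. It nowhere defines a negative outcome as a non-significant test, the analysis sections contain no such reading, and the phrase pairing positive with significant only triggers the economic analysis. This part of the reply stands. What remains is the parenthesis itself, which explains a negative outcome as no effect.

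A reader might also infer that the blinded interpretation scheme has no criterion for null results. That cannot be asserted: the article only summarises a cited scheme that is not at hand, and a full protocol or analysis plan may say more. The summary does show that the interpretation is frozen at unblinding, so any criterion has to be in place by then.

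Nor does the article say that a negative result will end the use of PRP in ankle osteoarthritis altogether. It speaks of widespread use, and says that generalisability to other products and regimens is unknown.

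Finally, the size should not be overstated. The window is narrow, because power for 12 points is about 93%. If PRP has no effect, about 95% of non-significant results exclude 12. The 65% at a true difference of 12 is a share of a 6.6% event, about 4% of all trials. The planned repeated-measures model on changes from baseline, with covariate adjustment, could narrow the interval and close the window. All of this stands, and it limits the size of the point. It does not make no effect a supported conclusion, since smaller benefits remain possible even when 12 is excluded.

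**Conclusion.** The concern holds as a point about the stated conclusion. Reading a negative outcome as no effect goes beyond what a superiority comparison can show. On the stated inputs, observed differences of about 5.2 to 6.8 points would be non-significant without excluding the trial's own 12-point difference. This occurs in about 4% of trials at a true difference of 0, 19% at 6 and 4% at 12. These figures assume 45 evaluable patients per group, an SD of 16.3, an unadjusted two-group comparison and a normally distributed estimate. They grow with a larger SD and vanish at an effective SD of about 14.3 or lower.

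A reader might go further and conclude that the trial is too small or that its test is wrong. The figures do not support that: a null result will usually be informative about 12 points. The correction is minor.

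**What to change.** Reword the sentence in the strengths-and-limitations list and its counterpart in the Discussion so that the conclusion depends on the 95% confidence interval of the 26-week AOFAS difference (PRP minus placebo). Enter the same rule in the blinded interpretation document before the code is broken:

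1. Interval wholly above 0: PRP superior, with clinical relevance judged against 12 points.
2. Interval includes 0 and its upper limit is below 12: a 12-point benefit is excluded. This is not to be worded as no effect.
3. Interval includes both 0 and 12: inconclusive.
4. Interval wholly below 0: PRP worse than placebo.

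Because the important difference is not agreed, also report the interval against the cited range of 10 to 15 points.

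The cost is a few sentences. No data, patients, test or sample size change. The downside is that some null results will have to be called inconclusive.

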## Background and rationale

Platelet-rich plasma (PRP) is a potentially efficacious treatment for ankle osteoarthritis (OA), but its use has not been examined in high-quality studies. Ankle OA is more common than hip or knee OA in the young active population.^1^ The incidence of symptomatic ankle OA is estimated to be 3.4% in the general adult population.^1^ Patients with ankle OA have a quality of life and physical functioning comparable with hip OA, end-stage kidney disease or congestive heart failure.^2^ These relatively young (predominantly female) patients have an increased risk for decreased work participation and family care. The available surgical intervention (arthrodesis) is associated with significant functional limitations. In contrast to hip and knee OA, where joint replacement is an excellent surgical alternative for severe cases, there is a clear need for effective non-surgical interventions in ankle OA.

PRP is defined as plasma containing a concentration of at least 1 000 000 platelets/μL.^3^ Growth factors are stored in α-granules within platelets, and are released in a selective manner on activation. Growth factors released from the α-granules of platelets are assumed to provide the regenerative benefits of PRP.

Recent reviews concluded that in animal models PRP can diminish multiple inflammatory interleukin (IL)-1-mediated effects.^4^ Due to this local anti-inflammatory response, PRP might have an indirect analgesic effect. The second suggested effect might be protection of the cartilage from destructive pro-inflammatory ILs. This is mediated due to an increased messenger RNA expression of proteoglycan core protein in the articular cartilage and decreased chondrocyte apoptosis.^4^ Consequently, PRP could positively influence the collagen network of the cartilage.

Recent systematic reviews on the intra-articular injection therapy in ankle OA found a lack of evidence from high-quality studies to assist in clinical decision-making.^5 6^ When compared with placebo injections, hyaluronic acid or corticosteroid injections, PRP injections might significantly decrease pain and improve function in patients with knee OA.^7–9^ Given the clinical effect on pain reduction in knee OA and a good safety profile, PRP is a promising non-surgical therapy for ankle OA.^10 11^ PRP might delay the irreversible surgical options like arthrodesis. No significant adverse events have been reported in any PRP trials regarding ankle OA, knee OA, acute hamstring injuries or Achilles tendinopathy.^8 12–17^ Clinical studies on PRP in ankle OA are limited to a single report of 5 cases and a prospective case series of 20 subjects, which both showed safety and significant reduction of pain at a mean of 16 months and 12 weeks follow-up.^14 18^ Well-designed prospective randomised controlled trials (RCT) have not yet been performed.

## Methods and design

### Objectives

We aim to determine the efficacy of PRP injections in the management of ankle OA by comparing two groups, both receiving two injections of either PRP or placebo solution. We hypothesise that PRP injections are efficacious for symptom reduction and functional improvement compared with placebo in the treatment of ankle (talocrural) OA.

### Study design

The Platelet-Rich plasma Injection Management for Ankle OA (PRIMA) study is a multicentre, stratified, block‐randomised, double‐blind, placebo‐controlled trial design will be conducted in order to compare two treatment groups: PRP versus placebo (saline). After the 26 weeks follow-up of the last patient in the study, the principal investigator and coordinating researcher will be unblinded only after the analysis of the primary outcome. A flow chart of the design and follow-up is shown in figure 1. The study included its first patient in August 2018 and aims to include the last patient by January 2021, consequently allowing analysis and then deblinding to commence after the last follow-up (26 weeks) of the last patient by July 2021.

**Figure 1 F1:**
[figure not shown]
Illustrating the Platelet-Rich plasma Injection Management for Ankle OA multicentre randomised controlled trial design and follow-up procedure. AOFAS, American Orthopaedic Foot and Ankle Society; OA, osteoarthritis.

### Patient involvement

#### Active patient involvement through reviewing the proposal (reviewer level)

Active involvement of patients during the design phase was performed by two patients with ankle OA. Both reviewed the grant proposal and provided feedback.

#### Execution phase: patients will actively contribute

Active patient involvement will be secured by invitation of at least two patients for the annual trial monitoring and evaluation meetings (informant level).

#### Analysis phase: patient will review and interpret the results (reviewer level)

Using the blinded codes of the randomisation groups and after breaking the randomisation code, patients (also active in the design phase) will be given the opportunity to interpret the results from a patient perspective.

#### Dissemination phase: patient-oriented approach (advisor level)

Results and new knowledge will be disseminated through the Dutch Arthritis Association (ReumaNederland), the Dutch patient federation, conferences and published in a scientific peer-reviewed journal. Dissemination activities will comprise a social media strategy with active patient involvement to share results with online patient communities and an events attendance strategy enabling patient participation in seminars, conferences and workshops.

### Study population

#### Population (base)

Patients with ankle OA in University Medical Centres, teaching hospitals, general hospitals and private specialist clinics will be informed about the study. In order to participate, patients must meet the eligibility criteria documented below.

### Inclusion criteria

Severity of ankle OA pain on a Visual Analogue Scale (VAS 0–100 mm) ≥40 mm during daily activitiesX-rays (anteroposterior (AP) and lateral view) indicating ≥grade 2 talocrural OA on the van Dijk classification (clarified under the ‘Radiographs’ section).^19^
Age≥18 years.

### Exclusion criteria

Patient has received injection therapy for ankle OA in the previous 6 months.Patient does not want to receive one of the two therapies.Patient has clinical signs of concomitant OA of one or more other major joints of the lower extremities that negatively affects their daily activity level.Previous ankle surgery for OA or osteochondral defects <1 year (not including surgery for an ankle fracture in the past).

### Radiographs

AP and lateral X-rays of the talocrural joints will be scored according to the van Dijk classification^19^:

Normal joint or subchondral sclerosis.Osteophytes without joint space narrowing.Joint space narrowing with or without osteophytes.(Sub)total disappearance or deformation of the joint space.

### Randomisation, blinding and treatment allocation

We will include patients at the centre of their first outpatient clinic appointment. For each patient the coordinating researcher will prepare a syringe with PRP and a syringe with placebo (isotonic saline: 0.9% sodium chloride). A Good Clinical Practice (GCP) approved data management system (Castor EDC, based in Amsterdam, the Netherlands) will be used to perform a computer-generated block randomisation scheme with patients stratified to centre with a variable block size of 2, 4 or 6. This procedure will ensure treatment allocation concealment. The coordinating researcher, treating physician and patient all remain blinded to the allocated intervention. An independent researcher from the coordinating location will have access to the randomisation result and the allocated intervention. This will be relayed to a GCP-certified research assistant at the centre. The research assistant then selects one of the two syringes based on the allocated intervention and blinds the syringe with a covering sheath, ensuring concealment of the content of the syringe. The patients, treating physicians and coordinating researcher will all be blinded to the allocation of the intervention and to the contents of the syringe. The success of blinding will be assessed by asking patients which injection they think they have received just after the injection procedure, this will then be registered accordingly.

After the 26 weeks follow-up of the last patient in the study, the principal investigator and coordinating researcher will be unblinded only after the analysis of the primary outcome. The patients will remain blinded to the therapy until the 52 weeks follow-up (online supplementary appendix 1) of the last patient in the study.

10.1136/bmjopen-2019-030961.supp1Supplementary data

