### Loss to follow-up

The coordinating researcher will attempt to limit loss to follow-up as much as possible by contacting every patient and being present at every patient visit. All digital questionnaires will be constantly monitored to ensure they are being filled in and otherwise followed up by the coordinating researcher. In the event of patient withdrawal, an analysis of demographic and prognostic characteristics will be done on these cases and the remaining patients. As previously described by Järvinen *et al*, we will document the patient eligible for and compliant with each follow-up.^24^

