### Statistical analysis

A standard operating procedure will be available to logically recode and clean the data. The data will be interpreted according to a blinded data interpretation scheme described by Järvinen *et al*.^24^ A statistical expert (SB) is present among the authors. The authors will interpret the statistical results until a consensus is reached. Once the authors are in agreement, the two groups will be unblinded and no changes will be made to the interpretation of the results.

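### The coordinating researcher, who contacts every patient, may be unblinded up to about six months before 52-week data collection ends; allocation should be withheld until those data are locked

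*Protocol article*

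**What the plan says.** All references are to the Protocol article.

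- **Timeline (Study design).** "The study included its first patient in August 2018 and aims to include the last patient by January 2021", with the schedule "allowing analysis and then deblinding to commence after the last follow-up (26 weeks) of the last patient by July 2021".
- **Who is blinded (Randomisation, blinding and treatment allocation).** "The coordinating researcher, treating physician and patient all remain blinded to the allocated intervention".
- **When the blind ends (same section).** For staff, "the principal investigator and coordinating researcher will be unblinded only after the analysis of the primary outcome". For patients the date is later: "The patients will remain blinded to the therapy until the 52 weeks follow-up" of the last patient enrolled.
- **Step before unblinding (Statistical analysis).** The authors first agree on a blinded interpretation. "Once the authors are in agreement, the two groups will be unblinded and no changes will be made to the interpretation of the results".
- **The coordinating researcher's tasks (Loss to follow-up).** This person limits attrition "by contacting every patient and being present at every patient visit", and pursues digital questionnaires that have not been completed.
- **Data due at 52 weeks (Table 1, under Inclusion).** AOFAS, the PROMs and the PRODISQ cost questionnaire. Questionnaires are sent electronically, and physical examination stops by 26 weeks.
- **Five years (Discussion).** "Our study will also evaluate the long-term efficacy of PRP for up to 5 years".

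**The concern.** The plan treats 52 weeks as a time point at which patients should still not know their treatment. Yet it allows the staff member closest to patients to learn the allocation up to about half a year earlier. The same plan takes considerable trouble at the injection visits (two syringes prepared, a covering sheath, separate disposal) to keep this person unaware.

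Three routes of influence are open for patients who have not yet reached 52 weeks: what is said during contact, how hard an incomplete questionnaire is pursued, and the scoring of any item that is not self-reported. Table 1 lists AOFAS apart from the PROMs, and the article does not say who scores it at 52 weeks.

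The data at stake are the 52-week AOFAS and PROMs, which are secondary outcomes, and the last part of the 12-month utility and cost data. Economic analysis describes that evaluation as needed after a positive result. The final cost and utility data could therefore be gathered by someone who knows both that result and the allocation.

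A related point concerns wording. The 5-year data are presented as evidence of long-term efficacy beside the double-blind, placebo-controlled label, although planned patient blinding will have ended by then.

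**Working it through.** **Inputs.** First inclusion August 2018, last inclusion January 2021, analysis and unblinding from July 2021 (Study design); 100 patients (Abstract). Two inputs are not in the article and are assumed: the accrual pattern, and the delay *d* in weeks between the last 26-week visit and unblinding.

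**1. The plan's own date.** 26 weeks = 182 days. Last inclusion on 1 January 2021 gives 2 July 2021; on 31 January 2021 it gives 1 August 2021. July 2021 is reproduced.

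**2. End of 52-week collection.** Last inclusion + 364 days gives 31 December 2021 to 30 January 2022. The window in which staff may know the allocation while 52-week data are outstanding is therefore 26 − *d* weeks.

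**3. Share of patients in the window, uniform accrual.** A patient's 52-week assessment falls after unblinding if the patient was enrolled in the last (26 − *d*) weeks of accrual. With accrual length *S* days:

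share = 7 × (26 − *d*) / *S*

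*S* lies between 854 days (31 August 2018 to 1 January 2021) and 914 days (1 August 2018 to 31 January 2021).

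| Delay *d* | Days in window | Share, *S* = 914 | Share, *S* = 854 |
|---|---|---|---|
| 0 weeks | 182 | 19.9% | 21.3% |
| 4 weeks | 154 | 16.8% | 18.0% |
| 8 weeks | 126 | 13.8% | 14.8% |
| 13 weeks | 91 | 10.0% | 10.7% |
| 26 weeks | 0 | 0% | 0% |

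With 100 patients, each percentage is also a number of patients.

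**4. Uneven accrual, no delay.** Let *f* = 182/914 = 0.199.

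- Rate rising linearly from zero: 1 − (1 − *f*)² = 1 − 0.801² = 0.36.
- Rate falling linearly to zero: *f*² = 0.04.

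Any delay lowers both figures.

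**5. Primary outcome.** The last 26-week value is collected, and the primary analysis done, before anyone named in the rule is unblinded. Primary outcome measure puts all follow-up time points in the model, but any 52-week values available at that analysis were also collected before unblinding.

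**6. Five years.** August 2018 + 5 years = August 2023 for the first 5-year assessment. This is later than both July 2021 (staff) and about January 2022 (patients), so on the planned timeline every 5-year value follows both unblinding steps.

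**The case against.** A reader might infer that the 52-week comparison is not double-blind for a fifth of patients. The article does not support this, for two reasons.

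- **Patients stay blinded.** They keep the blind until the last 52-week follow-up, and no early unblinding of treating physicians is stated. On the self-reported scales, completed electronically, the blinded patient is the rater. What remains is an indirect risk.
- **A fifth is the no-delay figure.** July 2021 is when analysis may start, with unblinding after it and after author consensus. The accrual pattern is also unknown. A fifth is the top of the range under uniform accrual, not a result.

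Three further points are fair. Attendance at every visit says little about 52 weeks, since physical examination ends by 26 weeks; contact and questionnaire follow-up are the tasks that clearly continue. Uneven pursuit of non-responders by arm is a possibility, not something the article shows, and all questionnaires are to be monitored. Finally, this is a condensed article: the full protocol may hand patient contact to others after the primary analysis, or unblinding of the groups may mean only that the group labels are revealed.

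These points limit the size of the problem but do not remove it. As published, the rule does not restrict what the coordinating researcher learns, and the article gives the same person the contact role throughout follow-up. If only group-level disclosure is meant, a sentence should say so.

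**Conclusion.** The point holds as an avoidable weakness in a stated rule, limited to secondary and economic data. Staff blinding may end up to 26 weeks before patient blinding, and one of the two people unblinded has continuing contact with patients.

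How many patients are exposed at 52 weeks cannot be read from the article. About 10–18% is a reasonable working range, resting on assumed uniform accrual and an assumed 4–13 weeks for analysis and consensus. The direction and size of any resulting bias cannot be calculated.

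On the 5-year data, a reader might infer that they must be kept out of the efficacy models. That goes too far. It is moot for the primary analysis, which is planned two years before the first 5-year assessment, and debatable for later secondary models. The plan states openly when patient blinding ends, and the Discussion does not claim that the 5-year comparison is blinded. What is supported is a matter of description: those results should not be presented as blinded, placebo-controlled efficacy.

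**What to change.** 1. In Randomisation, blinding and treatment allocation, state that patient-level allocation is withheld from the coordinating researcher, and from anyone else who contacts patients or handles their data, until the last patient's 52-week data are locked. Exposure at 52 weeks then falls to 0% whatever the accrual pattern or delay.
2. Report the 26-week result at group level only. A patient-level file carrying coded groups reveals every allocation once the codes are named, so that file should also stay with people who have no patient contact.
3. Wherever the 5-year results are announced or reported, describe them as unblinded follow-up of the randomised groups.

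**Cost.** The first two items need a change of wording and of data access. An independent researcher already holds the allocation, so no new role is required, and the 26-week report is not delayed. The coordinating researcher works from group-level results for up to about six more months. The third item is wording only.
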